## Abstract

**Background:**

A diet rich in fruits and vegetables is recommended for cardiovascular health. However, the majority of Australians do not consume the recommended number of vegetable servings each day. Furthermore, intakes of vegetables considered to have the greatest cardiovascular benefit are often very low. Results from prospective observational studies indicate that a higher consumption of cruciferous vegetables (e.g. broccoli, cabbage, cauliflower) is associated with lower cardiovascular disease risk. This may be due to the presence of specific nutrients and bioactive compounds found almost exclusively, or at relatively high levels, in cruciferous vegetables. Therefore, the aim of this randomised controlled crossover trial is to determine whether regular consumption of cruciferous vegetables results in short-term improvement in measures related to cardiovascular disease risk, including ambulatory blood pressure, arterial stiffness, glycaemic control, and circulating biomarkers of oxidative stress and inflammation.

**Methods:**

Twenty-five participants (50–75 years) with mildly elevated blood pressure (systolic blood pressure 120–160 mmHg) will complete two 2-week intervention periods in random order, separated by a 2-week washout period. During the intervention period, participants will consume 4 servings (~ 300 g) of cruciferous vegetables per day as a soup (~ 500–600 mL/day). The ‘control’ soup will consist of other commonly consumed vegetables (potato, sweet potato, carrot, pumpkin). Both soups will be approximately matched for energy, protein, fat, and carbohydrate content. All measurements will be performed at the beginning and end of each intervention period.

**Discussion:**

The findings of this study will provide evidence regarding the potential cardiometabolic health benefits of cruciferous vegetables, which may contribute to the revision of dietary and clinical guidelines.

**Trial registration:**

The trial was registered with the Australian New Zealand Clinical Trial Registry on 19th September 2019 (ACTRN12619001294145).

## Background

Cardiovascular disease is the leading cause of death in Australia, accounting for 27% of all deaths in 2017 [1]. Furthermore, cardiovascular disease is the largest disease contributor to Australian health expenditure, costing the healthcare system approximately $5 billion (11%) each year [2]. One of the most important modifiable risk factors for cardiovascular disease is an unhealthy diet [3]. It is recommended that individuals consume high amounts of vegetables, fruits, mono- and polyunsaturated fatty acids, and fibre, whilst limiting their intake of total and saturated fat, cholesterol, and salt. Like cardiovascular disease, the prevalence of type 2 diabetes is increasing worldwide [4]. Adults with type 2 diabetes have a two- to three-fold increased risk of experiencing a heart attack or stroke [5]. Factors such as high blood pressure, high blood cholesterol, and overweight and obesity play a major role in the development of cardiometabolic diseases, further highlighting the importance of a healthy diet to assist in the maintenance of these factors within healthy parameters [6].

Despite knowledge of the importance of vegetables in the diet and the inclusion of such recommendations in dietary guidelines [7], only 7.5% of Australian adults consume the recommended 5–6 daily servings of vegetables (375–450 g) [8]. This is similar in many other countries [9, 10]. Inadequate vegetable intake has been attributed to 17 and 10% of the total burden of stroke and coronary heart disease, respectively [11]. In Australia, it has been estimated that total health expenditure could be reduced by $1.4 billion per year if Australians consumed the recommended 5–6 servings of vegetables daily [12].

Although current dietary guidelines recommend a high intake of all vegetables, evidence suggests that not all vegetables offer equal health benefits. In particular, studies have shown that some vegetables may be more protective against cardiovascular disease than others. Results of prospective observational studies indicate that higher consumption of vegetables from the Brassicaceae family (also called Cruciferae, known as cruciferous vegetables) is associated with lower cardiovascular disease risk [3, 13–15]. These vegetables are commonly known as cruciferous vegetables and include broccoli, cabbage, cauliflower, Brussels sprouts, kale, and bok choy. There are a number of nutrients and bioactive compounds found almost exclusively, or at relatively high levels, in cruciferous vegetables. These include, but are not limited to, organosulfur compounds, nitrate, and phylloquinone (vitamin K1). Recent studies have highlighted the potential cardiovascular health benefits of these compounds [13–18].

Extensively studied for their anti-cancer properties [15], organosulfur compounds have also been reported to have potential cardiovascular health benefits [13–15]. These compounds may slow atherosclerotic plaque progression through a reduction in inflammation and reactive oxygen species [15]. In addition to the potential benefits of organosulfur compounds found in cruciferous vegetables, nitrate has been shown to reduce blood pressure in healthy populations [19] and potentially lower the risk of cardiovascular disease clinical endpoints [16–18]. Through the enterosalivary nitrate-nitrite-nitric oxide pathway, dietary nitrate is reduced to nitrite in the oral cavity, which then enters the circulation upon swallowing and is converted to nitric oxide; a cell signalling molecule important in regulating vascular tone and integrity [20]. Currently, there is limited evidence regarding dietary phylloquinone intake and cardiovascular disease. However, some studies have suggested an inverse relationship [21, 22] and there is emerging evidence of the potential role of phylloquinone in inhibiting vascular calcification [23].

If cruciferous vegetables are indeed more superior than other vegetables in lowering risk of cardiovascular disease then targeted dietary modification including an increased intake of cruciferous vegetables has the potential to play an important role in cardiovascular disease prevention. Overall, further evidence is required to evaluate the cardiovascular health benefits of cruciferous vegetables and their bioactive constituents. Intervention studies are needed to establish the benefit of these vegetables on cardiovascular health and to determine whether cruciferous vegetables are superior to other more commonly consumed vegetable types. At present, there are no intervention trials comparing the cardiovascular health benefits of these vegetable types. The proposed study will establish the efficacy for an increase in cruciferous vegetable intake to improve measures related to cardiovascular disease risk, including blood pressure, glycaemic control, oxidative stress, and inflammation.

## Methods

### Objectives

#### Primary objective

To determine if cruciferous vegetables are superior in lowering blood pressure than more commonly consumed vegetables in middle-aged and older adults with mildly elevated blood pressure.

#### Secondary objectives

To determine if cruciferous vegetables are superior in improving arterial stiffness, glycaemic control, oxidative stress, and inflammation than more commonly consumed vegetables in middle-aged and older adults with mildly elevated blood pressure.

### Research hypotheses

The study aims to test the following hypotheses:
Daily consumption of cruciferous vegetables, in comparison to other commonly consumed vegetables, will lower ambulatory blood pressure in middle-aged and older adults with mildly elevated blood pressure.Daily consumption of cruciferous vegetables, in comparison to other commonly consumed vegetables, will improve arterial stiffness, glycaemic control, and circulating biomarkers of oxidative stress and inflammation in middle-aged and older adults with mildly elevated blood pressure.

### Trial design

The VEgetableS for vaScular hEaLth (VESSEL) study protocol adheres to the Standard Protocol Items: Recommendations for Intervention Trials (SPIRIT) 2013 Statement (**see** Additional file 1) [24, 25]. The VESSEL study is designed as a randomised, controlled, crossover trial with two 2-week dietary intervention periods, separated with a 2-week washout period. Participants will be randomly assigned (1:1) to one of 2 sequence orders using computer generated random numbers. All participants will complete both dietary interventions. Therefore, as participants will act as their own control, this will remove any potential differences between subjects and reduce the potential bias when estimating the intervention effect. A detailed process evaluation will be performed to assess the suitability, reliability, and implementation of all procedures involved in this study (protocol in preparation).

### Participants, interventions, and outcomes

#### Study setting

This study will be conducted at the Royal Perth Hospital Research Foundation, School of Medical and Health Sciences, Edith Cowan University. The Royal Perth Hospital Research Foundation is located in Perth CBD, Australia.

#### Eligibility criteria

Participants must provide written informed consent before any physical assessments occur (see Additional file 2 for sample Participant Information and Consent Form).

##### Inclusion criteria

We will recruit ambulant community-dwelling men and women aged between 50 and 75 years who have mildly elevated blood pressure (systolic blood pressure 120–160 mmHg, inclusive, and diastolic blood pressure < 100 mmHg).

##### Exclusion criteria

Volunteers will be excluded from participation based on the following criteria: body mass index < 18.5 or ≥ 40 kg/m^2^; systolic blood pressure > 160 mmHg or < 120 mmHg; diastolic blood pressure > 100 mmHg; use of > 2 antihypertensive medications or irregular use of nitric oxide donors, organic nitrites and nitrates, and sildenafil and related drugs; diagnosed diabetes or fasting blood glucose > 6.5 mmol/L; fasting total cholesterol > 8 mmol/L; current or recent (< 12 months) smoking; adhesive allergy; regular aspirin use; medication use for thrombosis or anticoagulants (Warfarin); history of cardiovascular or peripheral vascular disease (myocardial infarction, stroke, transient ischaemic attack, amputation due to arterial insufficiency, any form of arterial revascularisation, history of exertional angina or claudication); psychiatric illness or other major illnesses, such as cancer; alcohol intake > 100 g per week; current or recent (within previous 6 months) significant weight loss or gain (> 6% of body weight) or actively trying to lose weight; pre-menopausal women; inability to attend clinic/office visits; use of antibiotics (within previous 2 months); use of antibacterial mouthwash and not willing to cease for trial duration; reported participation in night shift work during the study period; and inability or unwillingness to follow the study protocol. Volunteers with specific dietary requirements, allergies, or intolerances (e.g. following a low FODMAP diet) that will interfere with their ability to follow the dietary requirements of the study will also be excluded.

#### Recruitment

Study investigators will continue to recruit participants until an approximately equal proportion of males and females have been enrolled. The enrolment period will extend over 6 months or until adequate sample is reached.

##### Recruitment strategy

Participants will be recruited through a wide range of state and local media channels including newspaper advertisements, media articles, and radio interviews. All advertisements will have prior approval from the Edith Cowan University Human Research Ethics Committee. Responses to inquiries about participation will be answered by the study coordinator ([name]) or a research assistant using a dedicated mobile phone or email address that will be operational during business hours. Volunteers interested in participating will be sent an information pack that explains the study in detail. The study coordinator ([name]) or a research assistant will provide verbal consent from interested volunteers willing to participant to be pre-screened over the telephone. Participant will be pre-screened to determine eligibility for further physical screening at the Royal Perth Hospital Research Foundation, Perth, Australia. Physical screening will include anthropometric measurements (height and weight), blood pressure measurements, an electrocardiogram, and a fasting blood test (lipid profile and glucose test). Blood pressure will be assessed at this clinic screening visit using a CARESCAPE™ Dinamap v100 Vital Signs Monitor (GE Healthcare, Buckinghamshire, UK). Participants will be asked to rest for 5 min before 5 blood pressure and heart rate readings taken at 2-min intervals. The first measurement will be excluded and the mean of the next 4 consecutive readings will be used to determine resting blood pressure. If blood pressure is found to be outside the eligible range, volunteers will be excluded from the study and will not undergo an electrocardiogram or a fasting blood test.

#### Sample size

A sample size of 25 participants completing the trial has been calculated based on the primary outcome of mean 24-h ambulatory systolic blood pressure. To allow for up to 10% withdrawal rate, we plan to recruit 28 eligible participants to this study. We have estimated > 90% retention based on our previous studies [26]. With α = 0.05, 25 participants will provide > 90% power to detect a 2.5 mmHg difference in mean 24-h ambulatory systolic blood pressure. The power calculation is based on an SD of 14 mmHg for systolic blood pressure, a within-period correlation between systolic blood pressure measurements of 0.6, a between period correlation of the mean systolic blood pressure of 0.6, and a minimum of 40 BP measurements over each 24 h period (up to 3 measures each hour 6 am-10 pm and up to 2 each hour 10 pm-6 am) [26]. This calculation utilises the variance inflation factor (VIF) formula for a cross-over trial of VIF=N*(1-ρ)/m, where N is the number of subjects required for a parallel design, ρ is the between period correlation (0.6), and m = 2 is the number of visits per subject [27]. With α = 0.05, 25 participants will also provide > 90% power to detect a 0.30 mmol/l (~ 5%) difference in mean 2-h post-meal estimated blood glucose concentration. This is based on within-group SD of 1.5 mmol/L and a minimum of 80 glucose measures (2 meals per day with soup, for 14 days, with a measure every 15 min over 2 h) over each 2-week period, and a within-subject correlation between measures of r = 0.6.

### Assignment of interventions

#### Allocation

##### Sequence generation

Eligible participants will be randomly assigned to one of 2 sequence orders with a 1:1 allocation using computer generated random numbers.

##### Concealment mechanism

Fifty sealed opaque envelopes, numbered 1–50, each containing one of the 2 sequence orders for intervention diets will be used for randomisation by opening an envelope, in consecutive order, as participants are entered into the study. The computer-generated random numbers and sealed opaque envelopes will be completed and held by a person independent of study investigators.

##### Implementation

The study coordinator will contact the person independent of study investigators to obtain the next available envelope once an individual is deemed eligible. The envelope will be opened and the code will be recorded.

#### Blinding

Due to the nature of the interventions given, participants cannot be completely blinded to the interventions received. Participants will be blinded to which soup is the active or control. However, both soups will be different in taste and appearance. Blinding will be used for all laboratory analyses.

#### Dietary interventions

Eligible participants will complete two 2-week dietary interventions separated by a 2-week washout period where participants will return to their usual diet. During each 2-week intervention period participants will consume standard lunch and dinner meals that will be provided to standardise background diets.

The two 2-week dietary interventions will correspond to:
Cruciferous vegetables (**CRV**, active): 4 servings (~ 300 g) of cruciferous vegetables (broccoli, cabbage, cauliflower, and kale) per day consumed as a soup at lunch and dinner (~ 500–600 mL soup/day); andother commonly consumed vegetables (**OCV**, control): 4 servings (~ 300 g) of other commonly consumed vegetables (potato, sweet potato, carrot, and pumpkin) per day consumed as a soup at lunch and dinner (~ 500–600 mL soup/day)

Four servings of vegetables (~ 300 g) daily represents an achievable daily intake of these vegetables. It is expected that participants will have a background vegetable intake of approximately 1–4 servings (~ 75–300 g) per day during the intervention periods. Therefore, the additional 4 servings of vegetables that the soups provide will shift vegetable intake to at or above the recommended 5–6 servings (375–450 g) per day.

Both active and control soups will be matched for energy (~ 600 kJ per serving). All vegetables will be boiled prior to blending into soup. A small amount of potato starch will be added to the CRV soup to approximately match the carbohydrate content with the OCV soup. There will be small differences in macronutrient content per serving: protein (CRV ~ 10 g, OCV ~ 5 g), fat (CRV ~ 0.6 g, OCV ~ 0.3 g), carbohydrate (CRV ~ 19 g, OCV ~ 27 g), and fibre (CRV ~ 9 g, OCV ~ 6 g).

Soups will be prepared at Edith Cowan University, Joondalup Campus, using standardized recipes and frozen immediately for storage.

To limit background diet variation, participants will consume frozen pre-prepared lunch and dinner meals provided by study investigators. These meals will provide approximately 1–4 servings (75–450 g) of background vegetables per day. Slight variation in vegetable intake between participants may occur, as participants will be able to select meals based on personal preference. With the exception of the intervention soups, participants will be asked to consume the same foods during both intervention periods. Participants will also be asked to replicate exactly what they ate in the 24 h prior to each clinic visit. This will allow us to directly compare the two vegetable types in both intervention periods.

Two consumer representatives provided feedback on the feasibility and palatability of the intervention soups. Consumer Advocate, [name], from the Consumer and Community Health Research Network assisted in finding the most appropriate consumer representatives. Both consumers (male and female) attended the Royal Perth Hospital Research Foundation, Perth, Australia, for 1 hour. Each consumer was provided with a $35 honorarium.

##### Modifications

In the unforeseen circumstance that a study participant needs to discontinue an assigned intervention, whenever possible the participant will be retained in the trial to enable follow-up data collection and prevent missing data. Before re-commencing the assigned intervention, participants will undergo a washout period.

##### Adherence

Food and nutrient intake will be assessed daily throughout the intervention periods using dietary records. Participants will be asked to record their entire food and beverage intake each day using the application “Research Food Diary” (Xyris Software, Brisbane, Australia) or via a paper-based record. We will also use self-reported soup intake diaries and ask participants to return their empty soup containers as a measure of soup compliance.

We will measure plasma carotenoids using high performance liquid chromatography [28, 29]. Plasma carotenoids will be measured as a biomarker of vegetable intake [30]. It is expected that total plasma carotenoids will be increased substantially after both the CRV and OCV interventions. However, the carotenoid profiles will vary slightly due to the differences in individual carotenoids present in the different vegetables consumed. S-methyl cysteine sulfoxide concentration in plasma samples will be used as a biomarker of CRV intervention and will be measured using liquid chromatography-mass spectrometry (LC-MS)/MS techniques as previously described [31]. It is expected that plasma S-methyl cysteine sulfoxide concentration will be increased after CRV intervention, but not OCV intervention, and is therefore a measure of CRV intervention compliance.

##### Concomitant care

Participants will be asked to take regular medications as per usual and refrain from participating in any other research studies whilst undergoing study requirements. If a participant is a regular blood donor, the individual will be asked to postpone donating blood until after the study has been completed.

#### Participant timeline

A schematic diagram of the trial design, procedures, and stages is shown in Fig. 1. The trial consists of two 2-week intervention periods, separated by a 2-week washout period. Participants will attend 12 morning clinic visits at the Royal Perth Hospital Research Foundation over a 6 to 7-week period. Outcome assessments will be taken at the beginning and end of each 2-week intervention.

**Fig. 1 Fig1:**
[figure not shown]
Schematic diagram of the trial design, procedures, and stages

#### Outcomes

##### Primary outcome

The primary outcome of this study will be the difference between interventions (CRV, OCV) for 24-h ambulatory brachial systolic blood pressure with the additional adjustment for pre-treatment systolic blood pressure.

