#### Statistical methods

Statistical analyses will be performed using IBM SPSS Statistics for Windows, version 25.0 (IBM Corp., Armonk, NY, USA) and STATA, version 16.0 (Statacorp, College Station, TX, USA). Statistical significance will be set at a 2-sided Type 1 error rate of *P* < 0.05. Descriptive statistics of normally distributed continuous variables will be expressed as mean ± standard deviation (SD), non-normally distributed continuous variables as median and interquartile range, and categorical variables as number and proportion (%). The primary analyses will be performed according to a modified intention to treat protocol and will include all randomised participants for which baseline data is obtained. Multilevel models will be used to assess the effect of the dietary interventions and these will produce unbiased estimates of the intervention effects whenever there are small amounts of missing data (i.e. < 10%). Where there is > 10% missing data, multiple imputation will be used as a sensitivity analysis. Covariates will be adjusted for in analyses as necessary. Further exploratory analyses will be conducted on those participants who fully comply to intervention protocols (“per-protocol analyses”).

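### The primary model adjusts for pre-treatment SBP without fixing the covariate's form; a single common slope can cost precision in a crossover, and splitting the baseline protects against most of that loss

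*Protocol article*

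**What the plan says.** Under Primary outcome, the treatment comparison is made "with the additional adjustment for pre-treatment systolic blood pressure". Under Secondary outcomes, the same adjustment applies to every listed outcome except mean continuous glucose. Under Statistical methods, "Multilevel models will be used to assess the effect of the dietary interventions"; the random effects and the form of the baseline covariate are not described. Participant timeline and Data collection methods place the measurements at the start and end of each intervention period, so two pre-treatment values exist per person.

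Under Sample size, the assumptions are an SD of 14 mmHg, at least 40 readings per 24 h, "a within-period correlation between systolic blood pressure measurements of 0.6" and "a between period correlation of the mean systolic blood pressure of 0.6". No correlation is given between the pre- and post-treatment 24-h means.

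**The concern.** In a two-period crossover the soup effect is estimated from within-person differences. A baseline covariate helps that contrast only as far as a person's change in baseline between periods predicts their change in outcome. How well people with high baselines predict people with high outcomes is irrelevant to it, because the participant effect already removes that.

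A period-specific baseline entered as one covariate receives one slope, estimated from both sources. The between-person relation is usually the stronger, so it pulls the slope above the within-person value. The model then subtracts too large a multiple of the baseline difference and carries its noise into the soup effect. With 25 completers, precision is scarce. The same wording governs all the adjusted secondary outcomes.

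**Working it through.** **Inputs.** From Sample size: SD 14 mmHg, 40 readings, 0.6 among readings in a 24-h trace, 0.6 between periods for the mean, 25 completers, target 2.5 mmHg. From Statistical methods: two-sided 0.05. Assumed, because not given: the within-period pre-post correlation r of the 24-h means, varied from 0.55 to 0.98. Every cross-period correlation is set to c = 0.6.

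**The plan's own figure.** SD of a 40-reading mean = 14 × √((1 + 39 × 0.6)/40) = 10.93 mmHg. Unadjusted SE of the soup effect = 10.93 × √(2 × 0.4/25) = 1.96 mmHg. Power at 2.5 mmHg = Φ(2.5/1.96 − 1.96), about 25% (23% with the t distribution). The stated power above 90% is not reproduced. That is a separate matter, but it shows how little precision there is to spare.

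**Slopes.**
- Within-person: b_W = (r − c)/(1 − c). At r = 0.6 this is 0.
- Between-person: b_B = (r + c)/(1 + c). At r = 0.6 this is 1.2/1.6 = 0.75.
- Single slope b: in large samples it minimises log V_B(b) + log V_W(b), where V_B = 2(1 + c)(1 + b²) − 4b(r + c) and V_W = 2(1 − c)(1 + b²) − 4b(r − c). At r = 0.6 the solution is 0.548.

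**Variance of the soup effect relative to no baseline adjustment (large sample).**
- Single slope: 1 + b² − 2·b·b_W. At r = 0.6: 1 + 0.548² − 0 = 1.30.
- Split baseline: 1 − b_W². At r = 0.6: 1.00.

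Estimating the extra slope costs something with 25 participants, so the last three columns come from 20,000 simulated trials of 25 participants, fitted by REML with a random intercept.

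| r | b_W | single b | single vs none, large sample | single vs none, n = 25 | split vs none, n = 25 | split vs single, n = 25 |
|---|---|---|---|---|---|---|
| 0.55 | −0.125 | 0.477 | 1.35 | 1.36 | 1.04 | 0.76 |
| 0.60 | 0 | 0.548 | 1.30 | 1.32 | 1.05 | 0.79 |
| 0.65 | 0.125 | 0.614 | 1.22 | 1.23 | 1.03 | 0.84 |
| 0.70 | 0.250 | 0.676 | 1.12 | 1.11 | 0.98 | 0.88 |
| 0.75 | 0.375 | 0.735 | 0.99 | 0.99 | 0.90 | 0.91 |
| 0.80 | 0.500 | 0.791 | 0.84 | 0.85 | 0.79 | 0.93 |
| 0.90 | 0.750 | 0.898 | 0.46 | 0.46 | 0.46 | 0.99 |
| 0.98 | 0.950 | 0.980 | 0.10 | 0.10 | 0.10 | 1.03 |

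At r = 0.6 the SDs of the estimate are 1.96 (none), 2.25 (single slope) and 2.01 mmHg (split). The gap between single slope and split is worth 25 × (1 − 0.79), about 5 participants. Power at 2.5 mmHg is 23.1%, 19.6% and 22.3%. Type I error is about 5% for both adjusted models. Single-slope adjustment breaks even with no adjustment at r of about 0.75.

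**Correlation that decays with time.** The four measurements fall at about weeks 0, 2, 4 and 6. Take 0.6 at four weeks and geometric decay: √0.6 = 0.775 at two weeks and 0.6 × 0.775 = 0.465 at six. The within-person slope is (0.775 + 0.775 − 0.775 − 0.465)/0.8 = 0.387, and the single slope is about 0.775. Single slope versus none: 1 + 0.775² − 2 × 0.775 × 0.387 = 1.00. Split versus none: 1 − 0.387² = 0.85. In large samples the single slope gains nothing here, while the split gains about 15%.

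**The case against.** The strongest reply is that the article never states the single-slope model. A split baseline fits its wording equally well, and so does adjustment for the first baseline only, which would leave the within-person contrast untouched. An analysis plan that is not shown may settle the form. This stands: a reader might infer that the protocol has chosen a precision-losing model, and the text does not support that. What remains is that the adjustment is part of the primary outcome's definition and two baselines exist. The period-specific reading is the natural one, since the only outcome exempted from adjustment is also the only one without a measurement at the start of each period. One covariate with one slope is then the ordinary implementation.

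A reader might also infer that the loss follows from the protocol's own correlations, or that adjustment can only hurt. Neither is supported. The pre-post correlation is not stated, and above about 0.75 single-slope adjustment helps. The within-period 0.6 most naturally describes readings inside one 24-h trace. If it applied to every pair of readings in a period, pre and post, the two 40-reading means would correlate at 40 × 0.6/(1 + 39 × 0.6) = 0.98. Adjustment would then gain strongly, and the split would be about 3% worse than the single slope.

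Splitting is not free either. It takes one degree of freedom and, at r near 0.6, has about 5% more variance than no adjustment. Nor is this a validity problem: no bias is alleged, and the type I error is held.

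**Conclusion.** The point holds as a matter of specification and precision. The form of the baseline covariate is open, and the ordinary way of filling the gap can be inefficient. If the pre-post correlation of the 24-h means is near the stated between-period 0.6, single-slope adjustment has about 30% more variance than no adjustment, and the split about 20% less than the single slope. If it is 0.75 to 0.90 with cross-period correlations of 0.6, single-slope adjustment is neutral to clearly helpful, and the split still has roughly 10% (at 0.75) to 1% (at 0.90) less variance. Only near 0.98 is the split the worse of the two, by about 3%. The case for acting rests on that asymmetry, not on any claim that the loss will occur.

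The result assumes a random-intercept model, equal variances at the four time points and the correlation patterns shown.

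**What to change.** Add one sentence to Statistical methods, or to the analysis plan if it is silent: post-treatment SBP is modelled on soup, period, the participant's mean pre-treatment SBP and that period's deviation from this mean, with a random participant effect. Use the same form for every secondary outcome adjusted for pre-treatment values.

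Keep this within the multilevel model. With complete data it gives the same soup effect as regressing the post-treatment difference on the pre-treatment difference and sequence. That regression, however, would drop participants with only one period, whom the modified intention-to-treat set retains. State that for someone with a single baseline the mean is that value and the deviation is zero.

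The cost is the sentence, one degree of freedom, and the small variance penalties noted above (about 5% against no adjustment near 0.6, about 3% against the single slope near 0.98). The change does not repair the power stated under Sample size, which needs its own correction.
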